## Abstract

**Background:**

Total hip arthroplasty (THA) is very effective in alleviating pain, but functional deficits persist up to a year following surgery. Regardless of standard physiotherapy programs, significant additional muscular atrophy and weakness occur. Deficits in strength have serious adverse consequences for these patients with respect to physical function, the maintenance of independence, and the requirement for revision surgery. Progressive resistance training in rehabilitation following THA has been shown to significantly enhance muscle strength and function. The fundamental principle is to progressively overload the exercised muscle as it becomes stronger. Different strength training protocols have been used at different times in the postoperative phase, in group or individual practices, with major differences being in center-based and home-based programs with or without supervision. The primary objective of our study is to evaluate whether an early postoperative home-based strength training protocol can improve patient functional outcomes at 3 months and 1 year following surgery. Secondary objectives are the feasibility of the presented protocol for all elective THA patients and its safety.

**Methods/design:**

This study is a prospective multicenter randomized clinical trial to be conducted in the orthopedic departments of two Slovenian hospitals. In each hospital, 124 patients aged 60 or older with unilateral osteoarthritis, an ASA score between 1 and 3, a signed informed consent form, and no terminal illness disabling rehabilitation participation will be randomly assigned to the intervention or control group. THA with an anterior approach will be performed. All patients will receive current standard physiotherapy during hospitalization. Patients in the intervention group will also learn strength and sensory-motor training exercises. Upon discharge, all will receive USB drives with exercise videos, written exercise instructions, and a training diary. Physiotherapists will perform the assessments (physical tests and the maximal voluntary isometric contraction assessment), and patients will fill out outcome assessment questionnaires (the Harris Hip Score and 36-Item Short Form Health Survey) at baseline and 1, 3, and 12 months after surgery.

**Discussion:**

The main purpose of our study is to design a new standardized rehabilitation protocol with videos that will be effective, safe, and accessible to all Slovenian THA patients.

**Trial registration:**

ClinicalTrials.gov NCT04061993. Registered on 07 November 2019. Protocol ID: PRT_PhD. Version 1.

**Supplementary Information:**

The online version contains supplementary material available at 10.1186/s13063-022-06779-8.

## Background

Total hip arthroplasty (THA) is one of the most widely performed and clinically successful surgical procedures, and the number of THA operations is rapidly increasing [1–4]. The number of THA procedures is expected to continue rising worldwide due to the wide range of indications for the procedure, and the prevalence of osteoarthritis (OA) is expected to increase as the population ages; accordingly, intentions to improve the mobility of elderly people are expected to increase [1–3, 5, 6]. THA is intended not only to relieve pain but also to restore hip biomechanics. The restoration of hip biomechanics leads to a minimal number of functional deficits, secures the longevity of the implant, and improves the quality of life, mobility, joint stability, and locomotion [2, 7]. THA is very effective in alleviating pain, but functional deficits persist up to a year following surgery [3]. Addressing these functional deficits is increasingly important, and postoperative center- and home-based programs have proven beneficial [5]. As technology and surgical techniques have improved, patient expectations from THA have also increased, including an early return to normal physical activities and a recovery of functional independence [8]. Early targeted rehabilitation has been shown to reduce hospital length of stay (LOS) without increasing the complication rates after THA [7, 9–11]. Utilization of the direct anterior approach, which is performed in the internervous and intermuscular plane, enables a fast recovery with little pain after surgery and does not require postoperative precautions [12]. With the implementation of optimal multimodal perioperative care to enhance recovery, the average hospital LOS has additionally reduced [13–17]. A reduction in the hospital LOS has increased the need for an efficient exercise program beyond the initial standard rehabilitation program completed during hospitalization [6]. A disadvantage of these programs is the need for patients to exercise under the supervision of professional staff at a hospital or rehabilitation center. These programs are expensive due to the high costs associated with staff supervision, treatment, and transportation between locations and are unfriendly because of the need for transportation [6, 7]. Although there are many studies that have tested different rehabilitation protocols against the “standard” practice, no explicit definition of standard practice exists. Standard physiotherapy rehabilitation programs may comprise hip joint mobilization, strengthening of adjacent muscles without external loading or with low-resistance weight, and gait training [1–3, 18]. However, it is well known that regardless of a patient’s adherence to standard physiotherapy rehabilitation programs, significant additional muscular atrophy and weakness occur in his or her affected limb, which is often in deficit compared to the healthy limb in patients with unilateral OA prior to surgery [1, 3, 7, 11]. Suetta et al. found 13% and 9% reductions in the cross-sectional area of the quadriceps on the operated side at 5 and 13 weeks after THA, respectively, following the completion of a standard program [11]. Deficits in strength have serious adverse consequences for THA patients with respect to physical function, the maintenance of independence, and the requirement for revision surgery. Leg strength deficits have been associated with poor gait symmetry, slow walking speeds, impaired stair-climbing and chair-rising abilities, limited access to public transportation, and an exacerbated risk of falling and loosening of the prosthesis [1, 2, 4, 7, 11, 19, 20]. In contrast, progressive resistance training (PRT) is an effective method for inducing muscle hypertrophy and increasing muscle strength and functional performance in healthy and clinical populations, including elderly individuals [21]. PRT in rehabilitation following THA has been shown to significantly enhance muscle strength and function, and PRT has been shown to be the main factor in achieving significant functional improvements in rehabilitation programs used after home- or center-based programs after THA [2, 5, 11, 22]. First, studies with strength training programs after THA were conducted with patients who underwent surgery after femoral neck fractures [18, 23]. The key points of these studies were that PRT is safe and effective in geriatric rehabilitation after hip surgery; the patients’ strength, functional performance, and emotional state improve by physical training; and long-term continuation of the programs may prevent detraining effects [23]. The fundamental principle of PRT is to progressively overload the exercised muscle as it becomes stronger [22, 24]. Evidence-based recommendations for resistance exercise to improve strength and power are as follows: an exercise frequency of 2–3 times per week, an exercise intensity of 60–70% 1-repetition maximum (1-RM) for novice to intermediate exercisers, 8–12 repetitions, 2–4 sets, a rest interval of 2–3 min between sets with ≥ 48 h between sessions, and a gradual progression [21, 22]. Studies in patients who underwent elective THA because of unilateral OA had small sample sizes, but they indicated that there are benefits of strength training protocols, and no major adverse effects were noticed [2, 8, 11, 19, 22, 25]. Different strength training protocols were used at different times in the postoperative phase, either in group or individual practices, with major differences being in center- and home-based programs with or without supervision. Some studies comparing supervised home- and center-based rehabilitation programs for THA patients have found greater improvements in function and quality of life for home-based patients than for center-based patients [7, 26, 27]. Studies of unsupervised home-based exercise programs beyond the immediate postoperative rehabilitation period have also reported increases in hip muscle strength, walking speed, and function with respect to those in the postoperative rehabilitation period [7, 20, 28]. Furthermore, a home-based rehabilitation program with supervision in the early postoperative period has been shown to be less expensive and more accessible for THA patients than a center-based program [26, 28, 29]. The main shortcomings of all published research are small samples, wide variations in exercise protocols that make it impossible to compare them with each other and cost ineffectiveness of the protocols developed. The implementation of the new rehabilitation protocol also depends on the financial situation of society and the organizational capacity of the health system. Therefore, for our country, we cannot directly transfer the protocol from existing studies. In an aging society, independent, self-reliant individuals after THA are an invaluable benefit of such enhanced protocol, both in terms of the burden on the individual family and in terms of improving society as a whole. With better organized home-based rehabilitation, we can also further shorten the LOS in hospitals, perform more THAs, and shorten the long surgery waiting list, which is a major problem in our country.

In our hospital, we implemented a rapid recovery protocol for all THA patients in 2011. We continuously made changes, including improvements in the preoperative preparation of patients and their relatives with a multidisciplinary preoperative education program and the implementation of the direct anterior approach, shortening the patients’ hospital LOS from an average of 10 to 3 days and improving patient satisfaction. Inherently, the primary goal is safe mobilization, not functional optimization. To date, only minor changes have been made to the standard physiotherapy protocol, and there is still much room for improvement. Currently, patients receive written and pictorial instructions for standard home-based exercises. This existing standard physiotherapy protocol, which has been shown to be safe but probably not maximally effective, will serve as a comparator in the present study.

### Objectives

The primary objective of our study is to evaluate the efficacy of an early postoperative home-based strength training protocol — to assess whether it can improve patient functional outcomes at 3 months and 1 year following surgery. The secondary objectives are the feasibility of the presented protocol for all elective THA patients and its safety.

Our study also aims to assess patient satisfaction with enhanced targeted physiotherapy and to prepare a new standardized rehabilitation protocol with videos that will be effective, safe, and accessible to all THA patients.

## Methods/design

### Study design

The study is a multicenter randomized controlled trial comparing the effect of intensive early postoperative physiotherapy with the current standard of physiotherapy for patients undergoing elective THA for unilateral OA. General Hospital Novo mesto and Valdoltra Orthopedic Hospital are involved in the project, and the standard physiotherapy program for patients after THA is similar in both hospitals. All patients who will receive an anesthesiologist’s approval and will already be scheduled for surgery will be assessed for eligibility. An orthopedic surgeon will invite patients to participate and give oral and written explanations about the trial. Patients will be included in the study after signing a written informed consent form. After admission to the hospital, they will complete the routine preoperative outcome assessment questionnaires (Harris Hip Score (HHS) and 36-Item Short Form Health Survey (SF-36)) and have standard preoperative AP X-rays of both hips taken. Physiotherapists will perform the assessments: physical tests and an isometric muscle strength assessment. In both hospitals, the included patients will be randomized to either the intervention group (IG) or the control group (CG), and the surgeons and patients will be blinded to the randomization process. The procedure will be performed with the direct anterior approach only in the General Hospital Novo mesto by 1 surgeon and in the Valdoltra Orthopedic Hospital by 4 surgeons. Patients will be mobilized on the day of surgery. During the expected LOS of 2–5 days, all patients will receive current standard physiotherapy, oral analgesics, and cryotherapy. Patients in the IG will receive extra one-on-one training to learn strength and sensory-motor exercises. If the surgeon applies any limitations for a patient regarding rehabilitation after surgery, the patient will be excluded from the study. At discharge, patients in both groups will receive USB drives with exercise videos, written exercise instructions, and a training diary. Patients in the IG will also receive exercise aids for the strength and sensory-motor training. All patients will be followed up with regular phone calls concerning possible complications, completion of the training diary, and the clarity of the exercises. The patients will visit the hospital as usual after 1, 3, and 12 months following surgery. At each follow-up, the physiotherapists will perform assessments, and patients will fill out questionnaires. The patients will have a standard postoperative X-ray of the operated hip immediately after the surgery and AP X-rays of both hips after 1 year, so we will be able to compare measurements of the hip offsets of the operated and healthy hips and observe any changes regarding component position or osteolysis. At every follow-up, the surgeon and physiotherapist will ask the patient about any adverse effects or reasons for training cessation. The trial flowchart is displayed in Fig. 1.

**Fig. 1 Fig1:**
[figure not shown]
Trial flowchart

This paper is written according to the Standard Protocol Items: Recommendations for Interventional Trials (SPIRIT) 2013 Statement for the reporting of clinical trial protocols (Table 1, Additional file 1) [30, 31].

**Table 1 Tab1:**
[figure not shown]
SPIRIT figure [30, 31]: schedule and outcome measurements preoperatively and at 1, 3, and 12 months postoperatively

### Study population

#### Inclusion criteria

Patients undergoing elective primary unilateral THA for OAPatients older than 60 years at the time of surgeryPatients with the ability to watch exercise videos on a USB drivePatients with an American Society of Anesthesiologists (ASA) classification 1–3

#### Exclusion criteria

Patients undergoing primary THA for a diagnosis other than OA (aseptic femoral head necrosis, dysplastic hip, or others) or revision THAPatients with previous hip interventions (osteosynthesis, osteotomy…)Patients discharged to rehabilitation units or nursing homesPatients unable to consent and comply with the study protocol (diagnosed with dementia, mental disorders, poor preoperative physical status, neurological disorders, amputations, trouble walking with walkers or wheelchairs, or a painful hip or knee prosthesis in other joints).

#### Randomization procedures

Randomization will be performed in each hospital separately. Randomization will be made using a bespoke web-based randomization protocol. Patients will be randomized on a 1:1 ratio to intervention group A (with strength and sensory-motor training included) or control group B (with standard-of-care physiotherapy), regarding inclusion order. Physiotherapists and coordinators of the trial will be aware of the randomization procedure. Patients and orthopedic surgeons will be blinded, but they will be unblinded, if any safety issue or adverse effect arises.

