#### Sample size calculation

A power calculation was performed based on a clinically significant difference in gait speed of 0.10 m/s on the 4- or 10-m walk (10 MW) test using data from Perera et al. [32]. Based on a substantial meaningful change of 0.10 m/s between the interventional and control groups and standard deviation of 0.28 m/s, with a significance level of 5% and a power of 80%, a needed sample size of 124 patients in each group was estimated (248 patients in total). All patients from surgeons, participating in the study, will be assessed for eligibility. A total of 124 patients in each hospital will be randomized according to the procedure described above on a 1:1 ratio, so that there will be 62 patients in group A and group B in both hospitals.

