Before any statistical analysis, data will be tested for normal distribution using the Kolmogorov–Smirnov test (K–S test). With normally distributed variables, the analysis of variance for repeated measures (AnovaRM) with two factors (time × group) will be employed. It will test the differences in the effects of two different exercise protocols. AnovaRM will be used to analyze between-group differences in the score changes among all time points, represented by preoperative measurements (on admission to the hospital) and measurements 1, 3, and 12 months postoperatively. Afterwards, the initial AnovaRM, post hoc tests with AnovaRM (time × group) with two time points will be performed. Differences between all pairs of time points will be analyzed. Additionally, the paired samples *t*-test to test for in-group differences in the score changes between the pairs of time points and the independent samples *t*-test for between-group comparisons at the same time point will be calculated. The bivariate Pearson correlation will be calculated for testing the relationships between variables representing relative changes in the results between two different time points (e.g., post-treatment/baseline) for each group separately. To test the reliability of maximal voluntary isometric contraction measurements and the 8UG test, we will use the intraclass correlation coefficient (ICC) with the two-way mixed-effects model with absolute agreement. Data will be presented as the arithmetic mean and standard deviation. In the case of a non-normal distribution, data will be presented as the median and interquartile range, and nonparametric tests will be used respectively for comparisons of dependent and independent groups. Instead of AnovaRM, the nonparametric marginal model (nparLD, R-statistics) [47] will be used. T-tests for dependent and independent samples will be changed with Wilcoxon matched-pair signed-rank test and Mann–Whitney *U* test, respectively. The Pearson correlation will be substituted with the Spearman rank correlation. Adverse effects comparison among the two groups will be made by using the chi-square test. We will consider a *P* value less than 0.05 as significant for all measures and use a 95% confidence interval (CI). A significance level (alpha) of 0.05 will be tested with a two-tailed test.

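### Hospital is a stratification factor in the randomisation but is absent from every planned between-group analysis, which costs some precision if the hospitals differ

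*Protocol article*

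**What the plan says.** Under Randomization procedures: "Randomization will be performed in each hospital separately", and "Patients will be randomized on a 1:1 ratio to intervention group A" or to control group B. The Sample size calculation section repeats this at the level of numbers: "A total of 124 patients in each hospital will be randomized according to the procedure described above", "so that there will be 62 patients in group A and group B in both hospitals".

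Under Data management and analysis, for normally distributed variables, "the analysis of variance for repeated measures (AnovaRM) with two factors (time × group) will be employed". Of this model the article says: "It will test the differences in the effects of two different exercise protocols". Two-time-point versions of the same model follow as post hoc tests. In addition, "the independent samples *t*-test for between-group comparisons at the same time point will be calculated". For non-normal data the replacements are a nonparametric marginal model and the Wilcoxon and Mann–Whitney tests. Adverse effects are compared by a chi-square test. None of these carries a hospital term or is stratified by hospital.

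The Study design section names one surgeon at one hospital and four at the other, and says that "the standard physiotherapy program for patients after THA is similar in both hospitals".

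**The concern.** Randomising separately within each hospital with equal arms removes hospital differences from the comparison of arms. An analysis that ignores hospital still counts those differences as residual noise. The reported standard error is then larger than the true one, confidence intervals are too wide, the actual type I error falls below 5% and power is given away.

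A hospital effect is plausible. The surgeons differ, the standard programmes are described only as similar, and each patient is tested at their own hospital, including on a purpose-built strength device. The planned size also has little to spare: 124 per arm gives almost exactly 80% power.

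This is not a detail left for a later analysis plan. The article names the factors of its main model and gives their number as two.

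**Working it through.** **Inputs from the article.** Difference 0.10 m/s, SD 0.28 m/s, two-sided 5%, power 80%, 124 per arm, 62 per arm in each of two hospitals. The article does not give the difference D between hospital means, so a range is assumed. The calculations assume that the planned 62/62 split is achieved.

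**Step 1. Reproduce the plan's figure.** n per arm = 2 × (1.96 + 0.842)² × 0.28² / 0.10² = 123.1, rounded up to 124, as stated. With 124 per arm, SE = 0.28 × √(2/124) = 0.03556 and power = Φ(0.10/0.03556 − 1.96) = 80.3%.

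**Step 2. Effect of omitting hospital at a single visit.** Let w be the within-hospital SD. With two equal hospitals the overall variance is w² + D²/4.

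- True SE of the arm difference: w × √(2/124)
- SE reported without hospital: √(w² + D²/4) × √(2/124)
- Ratio r = √(1 + D²/(4w²))
- Actual type I error = 2 × (1 − Φ(1.96 r))
- Unadjusted power = Φ((0.10 − 1.96 × reported SE)/true SE)
- Adjusted power = Φ(0.10/true SE − 1.96)

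The article does not say whether 0.28 m/s includes variation between hospitals, so both readings are shown.

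*Reading A: 0.28 m/s is the overall SD.* The reported SE is 0.03556 throughout.

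| Hospital difference | w | SE too large by | Actual alpha | Unadjusted power | Adjusted power |
|---|---|---|---|---|---|
| 0.10 m/s | 0.2755 | 1.6% | 0.046 | 80.7% | 81.5% |
| 0.5 w (0.136 m/s) | 0.2716 | 3.1% | 0.043 | 81.0% | 82.6% |
| 0.8 w (0.208 m/s) | 0.2600 | 7.7% | 0.035 | 82.1% | 85.7% |
| 1.0 w (0.250 m/s) | 0.2504 | 11.8% | 0.028 | 83.0% | 88.2% |

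Unadjusted power also rises above 80% here. Part of the 0.28 is then hospital variation, which does not disturb a balanced comparison, so the true SE is smaller than the planning SE. The loss is the gap between the last two columns: 0.8, 1.6, 3.6 and 5.2 points.

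*Reading B: 0.28 m/s is the within-hospital SD.* Adjusted power is 80.3% throughout.

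| Hospital difference (m/s) | SE too large by | Actual alpha | Unadjusted power |
|---|---|---|---|
| 0 | 0% | 0.050 | 80.3% |
| 0.05 | 0.4% | 0.049 | 80.1% |
| 0.10 | 1.6% | 0.047 | 79.4% |
| 0.15 | 3.5% | 0.043 | 78.3% |
| 0.20 | 6.2% | 0.037 | 76.8% |
| 0.28 | 11.8% | 0.028 | 73.3% |

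**Step 3. The time × group test.** With two time points this is a test on change, and a hospital offset that is the same at both visits cancels. A simulation checked this (20,000 runs, within-hospital SD 0.28, assumed correlation 0.5 between visits):

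| Assumed hospital difference | Test | Unadjusted power | Adjusted power |
|---|---|---|---|
| 0.20 m/s, constant over time | t-test at follow-up | 76.4% | 79.8% |
| 0.20 m/s, constant over time | time × group | 79.7% | 79.7% |
| 0.20 m/s in change over time | time × group | 76.2% | 79.8% |

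The single-visit tests therefore lose power for any hospital difference at that visit. The main time × group test loses power only when hospitals differ in how patients change.

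**The case against.** The strongest reply is that the harm is conditional and mostly small. The hospitals share eligibility criteria, surgical approach and a similar standard programme, and nothing in the article shows that their outcomes differ. A difference of 0.5 to 1.0 within-hospital SD is about 0.14 to 0.25 m/s, or 1.4 to 2.5 times the 0.10 m/s that the article treats as a substantial change. At 0.10 m/s the loss is under one point. The main test compares changes over time, where a constant offset from site or assessor drops out, and the single-visit t-tests are introduced as additional. All of this stands, and it limits the size of the point.

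It does not remove the point. The article states a model that omits a factor on which it randomises, and including that factor costs almost nothing whether or not the hospitals differ.

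A reader might infer more than the documents support:

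- **That the comparison is biased or that false positives are inflated.** With balance within hospital, the arm difference is unbiased and the test errs towards caution.
- **That the trial is underpowered because of this.** If 0.28 m/s already includes hospital variation, the planned 80% is met in every scenario shown.
- **That missing results by hospital are a defect.** Such supportive analyses are commonly left to an analysis plan, and an interaction test with 124 patients per hospital would have little power.

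**Conclusion.** The point holds as one of efficiency and interval accuracy, not of validity. Randomisation is stratified by hospital and no between-group analysis reflects it. If outcomes differ between hospitals, the single-visit t and Mann–Whitney tests are conservative. For hospital differences from 0.10 m/s to one within-hospital SD, the t-test's standard error is 1.6% to about 12% too large and its true alpha lies between about 4.6% and 2.8%. The power given up is about 1 to 5 points if 0.28 m/s is the overall SD, and about 1 to 7 points (80.3% down to 79.4% and 73.3%) if it is the within-hospital SD. The time × group test shares the loss only where hospitals differ in change over time.

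The omission itself is certain. Its size is not: it rests on an assumed hospital difference, on achieving the planned 62/62 split, and on normal approximations for gait speed. The strength and 8-foot Up and Go measures were not calculated. With no hospital difference the loss is zero.

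**What to change.** - **Repeated-measures models, including the two-time-point post hoc versions:** add hospital and hospital × time as factors. A hospital main effect alone leaves the time × group test unchanged. Where the nonparametric marginal model is used instead, include hospital there as well.
- **Single-visit comparisons:** replace the independent-samples t-test by a linear model with group and hospital, and the Mann–Whitney test by a rank test stratified by hospital.
- **Adverse effects:** replace the chi-square test by a Mantel–Haenszel test stratified by hospital.
- **Optional:** report the arm difference by hospital, labelled supportive only.

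In the single-visit linear model the cost is one residual degree of freedom, from 246 to 245. No patients, visits or data are added and the sample size stays at 248. The article reports recruitment as ongoing at submission. The change should be fixed in writing before results by arm are examined, including at the interim analysis planned for the end of recruitment.

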
### Outcome measures

The primary outcome of the study is the efficacy of the chosen protocol, measured by physical tests. These comprise the 10 MW test, the 8-foot Up and Go (8UG) test, and isometric muscle strength. Secondary outcomes are the patient questionnaires, which will be used to draw conclusions about patient satisfaction and the feasibility of the protocols, and consistent recording of any adverse effects.

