### Data management and analysis

All data will be collected and stored in paper form by the corresponding author, who is responsible for the confidentiality of the data. All check-up forms will be printed and completed preoperatively and at every check-up by the physiotherapist and orthopedic surgeon. The questionnaires will also be printed and completed by patients. The corresponding author will enter the data into anonymized tables, which will then be used for statistical processing. The software program SPSS 21 (IBM SPSS Statistics for Windows, version 21.0. Armonk, NY: IBM Corp.) will be used for statistical analysis.

We will perform an intention-to-treat (ITT) analysis, which is an analytic strategy for reducing potential bias in treatment effects arising from missing data in randomized controlled trials. In ITT analysis, a study participant is analyzed as belonging to whatever treatment group he/she was randomized into, whether or not the treatment course was completed as intended. In case of missing data, sensitivity analyses will be performed and reported.

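### Unblinding the surgeon at any adverse effect means that patient's later events are recorded with the arm known

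*Protocol article*

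**What the plan says.** All places are in the protocol article.

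- **Blinding rule** (Randomization procedures): "Patients and orthopedic surgeons will be blinded, but they will be unblinded, if any safety issue or adverse effect arises". No degree of severity and no need for the allocation is attached to the trigger.
- **Who is not blinded** (same section): "Physiotherapists and coordinators of the trial will be aware of the randomization procedure". The physiotherapists also teach the intervention exercises, so they know each patient's arm.
- **Who asks** (Study design): "At every follow-up, the surgeon and physiotherapist will ask the patient about any adverse effects or reasons for training cessation". The visits are at 1, 3 and 12 months.
- **Who records** (Data management and analysis): "All check-up forms will be printed and completed preoperatively and at every check-up by the physiotherapist and orthopedic surgeon".
- **What the data are for:** safety is a secondary objective (Objectives: "The secondary objectives are the feasibility of the presented protocol for all elective THA patients and its safety"). The secondary outcomes include "consistent recording of any adverse effects" (Outcome measures). The analysis section adds: "Adverse effects comparison among the two groups will be made by using the chi-square test".

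**The concern.** Two kinds of staff collect adverse effects at the visits, and only the surgeon is blinded. The rule ends that blind automatically once a patient has any adverse effect, however minor. The surgeon then goes on asking the same patient about adverse effects, and filling in the forms, at the remaining visits.

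Whether a complaint counts as an adverse effect, how severe it is and what caused it are partly matters of judgement. A surgeon who knows that a patient is doing early strength training may record more events, by looking harder, or fewer, by regarding soreness as expected. Either would distort the chi-square comparison that serves the safety objective, and the direction cannot be told in advance.

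**Working it through.** The point concerns procedure, so most of the check is to read the sections together.

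**1. The plan's own figure.** The only computed design figure is 124 per group. With a difference of 0.10 m/s, SD 0.28 m/s, two-sided 5% and 80% power:

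n = 2 × (1.960 + 0.842)² × 0.28² / 0.10² = 2 × 7.849 × 0.0784 / 0.01 = 123.1, rounded up to 124.

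It reproduces (power at 124 per group is 80.3%). The point does not depend on it; 124 per arm is used only in step 4.

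**2. Following one patient through the rule.**

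- *Before any adverse effect:* the surgeon is blinded and the physiotherapist is not.
- *First event, reported to the surgeon at a visit:* the event precedes unblinding, so it can be recorded blind.
- *First event, surfacing elsewhere:* the regular phone calls ask about complications (Study design), the diary collects adverse effects (Training compliance), and severe pain prompts contact with the physiotherapist (the section on home-based training). Any of these can trigger unblinding before the surgeon completes a form.
- *Later events in the same patient:* the surgeon knows the arm at every remaining visit.

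This assumes that the surgeon's entries on the check-up forms feed the adverse-effect data. The text implies this but does not spell it out.

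**3. Which results are exposed.** The physical tests are performed by physiotherapists, who are unblinded from the start, so the surgeon's status changes nothing there. The exposed result is the comparison of adverse effects. If the chi-square test counts patients with at least one event, only first events matter, and the exposure is limited to those that surface before the surgeon's form is completed. If it counts events, all later events are exposed as well. The article does not say which unit is used.

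**4. Sensitivity, on assumed inputs only.** Take equal true rates, 124 patients per arm and an uncorrected chi-square test at 5%. Let one arm have a fixed multiple of the other arm's recorded rate. The exact binomial probability of a significant result is:

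| Assumed base rate | Ratio 1.0 | Ratio 1.2 | Ratio 1.5 |
|---|---|---|---|
| 10% | 5.0% | 7.9% | 22.2% |
| 20% | 5.2% | 12.1% | 44.8% |
| 30% | 4.9% | 17.2% | 68.8% |

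These ratios apply to a whole arm. If only a share f of an arm's events is recorded with the arm known, and those are recorded r times as often, the ratio for the arm is 1 + f(r − 1). An arm-wide ratio of 1.2 with r = 1.5 needs f = 0.2 / 0.5 = 0.4. The documents give neither f nor r. The table shows how sensitive the test is to differential recording; it does not estimate the bias from this rule.

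**The case against.** **The first event comes before the unblinding.** This stands. A reader might infer that the blind survives only in event-free patients, or that every event in the comparison is compromised. The rule does not support that: every patient is at risk of a first event, and where the surgeon is the first to hear of it the blind does its work. Only later events, and first events that surface elsewhere before the form is completed, are exposed.

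**Asking about training cessation need not reveal the arm.** This also stands. Both groups exercise at home with videos, written instructions and a diary, and an answer such as pain fits either arm. An answer may mention the aids or exercises that only the intervention group has, but that is an inference. The unblinding rule carries the point without it.

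**The X-rays.** Study design says the films at 1 year serve to "observe any changes regarding component position or osteolysis". A reader might infer that an unblinded surgeon judges them. No section names the reader of the films, and Outcome measures does not list these findings, so the inference is unsupported.

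**Physiotherapists collect the same data unblinded.** True, and it limits what the change can achieve. It also means that the surgeon's blind is the only one among these staff.

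**Unblinding for safety is normal, and an article leaves details out.** Unblinding where care needs it is not disputed. An unblinding log or the order of form entries could well be in the full protocol, and their absence here is no fault. The automatic trigger, however, is stated outright in the text, and following it as written has the consequence described.

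**Conclusion.** The concern holds for the rule as written. Automatic unblinding at any adverse effect removes the only blind among the staff who ask about and record adverse effects at the visits. It does so in patients who already have one event, and in some before that first event is written down.

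The consequence is possible bias of unknown direction in a secondary comparison. Its size cannot be derived: the documents give no adverse-effect rate, no split between first and later events, and no measure of differential recording. Differential recording is a risk and has not been shown. The surgeon's unblinding does not bear on the physical-test primary outcomes.

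The conclusion rests on two assumptions: that the surgeon's form entries feed the safety comparison, and that recording an adverse effect involves some judgement. The change is worth making because it costs little.

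**What to change.** 1. In Randomization procedures, replace the automatic trigger by unblinding, of surgeon or patient, only where the investigator judges that the allocation is needed for that patient. The investigators define when that is so.
2. Require the surgeon to write the event and its severity on the check-up form before any unblinding.
3. Log each unblinding with its date and reason.
4. Optionally, in Study design, let the physiotherapist, who already knows the arm, ask about reasons for training cessation, since the answers may reveal the arm to the surgeon.

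The cost is a change of wording, a brief judgement and one more form entry per event. No new staff are needed. Two limits remain. Recruitment began in 2018 and was still under way when the article was submitted, so events already recorded are not repaired. The physiotherapists' own recording also stays unblinded, so the safety comparison is only partly protected.
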